11. History of idiopathic pulmonary fibrosis (including pneumonitis), drug-induced pneumonitis, organizing pneumonia, or evidence of active pneumonitis on screening chest CT scan or interstitial lung disease with ongoing signs and symptoms at inclusion. History of radiation pneumonitis in the radiation field (fibrosis) is permitted,
12. Has known hepatitis B or hepatitis C active and/or treated by antiviral therapy,
13. Has a known history of Human Immunodeficiency Virus (HIV) (HIV1/2 antibodies) or known acquired immunodeficiency syndrome (AIDS)
14. Spot urine must not show 1+ or more protein in urine or the patient will require a repeat urine analysis. If repeat urinalysis shows 1+ protein or more, a 24-hour urine collection will be required and must show total protein excretion <1000 mg/24 hours,
15. Major surgical procedure or significant traumatic injury within 28 days before start of study medication,
16. Non-healing wound, non-healing ulcer, or non-healing bone fracture requiring orthopedic treatment,
17. Patients with evidence or history of any bleeding diathesis, irrespective of severity,
18. Any hemorrhage or bleeding event  $\geq$  CTCAE Grade 3 within 4 weeks prior to the start of study medication,
19. Arterial or venous thrombotic or embolic events such as cerebrovascular accident (including transient ischemic attacks), deep vein thrombosis or pulmonary embolism within 6 months before the start of study medication (except for adequately treated catheter-related venous thrombosis occurring more than one month before the start of study medication),
20. Ongoing infection > Grade 2 as per NCI CTCAE v5.0,
21. Uncontrolled hypertension (Systolic blood pressure > 140 mmHg or diastolic pressure > 90 mmHg) despite optimal medical management,
22. Congestive heart failure  $\geq$  New York Heart Association (NYHA) class 2,
23. Unstable angina (angina symptoms at rest), new-onset angina (begun within the last 3 months),
24. Myocardial infarction less than 6 months before start of study drug
25. Uncontrolled cardiac arrhythmias,
26. Pregnant or breast-feeding patients
27. Individuals deprived of liberty or placed under legal guardianship,
28. Prior organ transplantation, including allogeneic stem-cell transplantation,
29. Known alcohol or drug abuse
30. Vaccination within 4 weeks of the first dose of Avelumab and while on trial is prohibited except for administration of inactivated vaccines.

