| Grade 3 : Systolic BP $\geq 160$ mmHg or diastolic BP $\geq 100$ mmHg
OR
More than one drug or more intensive therapy than previously used indicated   | Hold treatment until diastolic BP $\leq 90$ mmHg, and if symptomatic, until symptoms resolve. When treatment is restarted, continue at the same dose level.

If BP is not controlled with the addition of new or more intensive therapy, reduce by 1 dose level.

If Grade 3 hypertension recurs despite dose reduction and antihypertensive therapy, discontinue therapy

Anti-hypertensive therapy: Treat with the aim to achieve diastolic BP $\leq 90$ mmHg:
- Start anti-hypertensive medication AND/OR
- Increase current antihypertensive medication AND/OR
- Add additional anti-hypertensive medications. | Hold treatment until diastolic BP $\leq 90$ mmHg, and if symptomatic, until symptoms resolve. When treatment is restarted, continue at the same dose level. |
| Grade 4 : Life-threatening consequences (eg, malignant hypertension, transient or permanent neurologic deficit, hypertensive crisis)                         | Discontinue therapy                                                                                                                                                                                                                                                                                                                                                                                                                                                                                                                                                                                                                           | No dose modification                                                                                                                                        |

a For cohort [A], regorafenib should be interrupted and no dose reduction are allowed. Patients requiring a delay of > 4 weeks should permanently discontinue regorafenib

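### Appendix 8 hypertension table: avelumab is held at Grade 3 but not at life-threatening Grade 4, and the Grade 3 restart condition can already be met when the hold begins

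*Protocol*

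**What the plan says.** The hypertension table in Appendix 8 gives a separate instruction for each drug at each grade.

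Grade 3 can be entered in two ways. One is by pressure: "Systolic BP $\geq 160$ mmHg or diastolic BP $\geq 100$ mmHg". The other is by treatment need, with no pressure value attached: "More than one drug or more intensive therapy than previously used indicated". The action for both drugs is then "Hold treatment until diastolic BP $\leq 90$ mmHg, and if symptomatic, until symptoms resolve", with restart at the same dose level. The regorafenib cell goes further. It requires antihypertensive drugs to be started, increased or added, calls for a one-level reduction if pressure is not controlled by new or stronger therapy, and stops regorafenib if Grade 3 recurs despite these steps. The avelumab cell has no such additions.

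Grade 4 is described as "Life-threatening consequences (eg, malignant hypertension, transient or permanent neurologic deficit, hypertensive crisis"). The regorafenib action is to "discontinue therapy". The avelumab action is "No dose modification".

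Section 7.6.2 adds general rules. Any toxicity may be managed by interruption or reduction if the investigator judges it appropriate. Severe toxicity should go to the principal investigator. Avelumab alone may continue after regorafenib is permanently stopped. A patient whose regorafenib is permanently stopped before the first avelumab dose (Cycle 1 Day 15) goes off study.

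**The concern.** A toxicity table is expected to be at least as cautious at a higher grade as at a lower one, or to say why it is not. In the avelumab column the lesser event carries a hold and the life-threatening event carries none. A site applying the table as written would withhold an infusion due during Grade 3 hypertension and would find no instruction to withhold one due during Grade 4.

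The second part concerns whether the Grade 3 hold can be applied at all. If a patient can satisfy the restart condition at the same reading that triggers the hold, the instruction has no content for that patient. Different sites will then act differently.

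Patient safety and consistent conduct are at stake, rather than inference. Held doses do bear on whether a cycle counts as complete for the efficacy-assessable population in section 10.2.2. That definition also admits patients with two incomplete cycles, however, and the document gives nothing from which to size any effect.

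**Working it through.** No arithmetic from the plan is involved. The check sets the cells side by side and asks two questions.

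**Does each drug's instruction stay level or tighten with grade?**

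| Grade | Regorafenib | Avelumab |
|---|---|---|
| 1 | continue | no change |
| 2 | continue; hold if symptomatic | no change |
| 3 | hold, then restart at same level; later reduction or stop if uncontrolled or recurrent | hold, then restart at same level |
| 4 | stop | no change |

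Regorafenib tightens throughout. Avelumab runs none, none, hold, none, so the step from Grade 3 to Grade 4 goes the other way. The Grade 4 phrase cannot be read as a silent hold at an unchanged dose. The same phrase at Grades 1 and 2 carries no hold, and where the table wants a hold with an unchanged dose (Grade 3) it says so.

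Other Appendix 8 tables do not show this pattern. For diarrhoea/colitis, rash, pneumonitis, Grade 1 to 4 endocrine disorders, raised creatinine and other immune-related events, the avelumab instruction tightens or stays level as grade rises. For hand-foot skin reaction it is unchanged at every grade listed.

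**Can the Grade 3 trigger and the restart condition hold at once?**

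Trigger: systolic ≥160, or diastolic ≥100, or more intensive therapy indicated. Restart: diastolic ≤90 and no remaining symptoms. Systolic pressure does not appear in the restart condition.

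| Asymptomatic patient (illustrative) | Grade 3 trigger | Restart condition |
|---|---|---|
| 165/85 mmHg | met, 165 ≥ 160 | met, 85 ≤ 90 |
| 150/88 mmHg, second antihypertensive needed | met through treatment need | met, 88 ≤ 90 |
| any systolic, diastolic ≥100 | met | not met, since 100 > 90 |

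The two sets overlap. Only a diastolic trigger or the presence of symptoms guarantees that the hold has some length. The wording is the same in both drug columns, so both drugs are affected.

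**The case against.** Several points limit the concern, and most of them stand.

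- *Avelumab monotherapy is allowed.* With regorafenib withdrawn at Grade 4, leaving avelumab unmodified can be read as not ending it. This accounts for the missing permanent stop. It does not account for a temporary hold at Grade 3, when regorafenib is also held, and none at Grade 4.
- *Not every Grade 4 event is affected.* If the event comes before Cycle 1 Day 15 and regorafenib is permanently stopped, section 7.6.2 takes the patient off study and no avelumab is given.
- *The table is not read alone.* Sections 5.2 and 7.6.2 let the investigator interrupt or stop treatment for unacceptable toxicity or in the patient's interest, and direct severe toxicity to the principal investigator. A reader might infer that sites will infuse avelumab during a hypertensive crisis. The document does not support that. It supports only that the table does not hold an infusion that falls due.
- *The diastolic target may be deliberate.* The same limit of 90 mmHg serves as the restart condition for symptomatic Grade 2, the restart condition for Grade 3, and the treatment aim at both grades. It is tempting to set it against non-inclusion criterion 21 in section 4.2, "Uncontrolled hypertension (Systolic blood pressure > 140 mmHg or diastolic pressure > 90 mmHg) despite optimal medical management", which uses both pressures. That criterion governs entry, not restart, so the two do not conflict.
- *The isolated systolic patient is not unmanaged.* The Grade 3 regorafenib cell still requires antihypertensive treatment and refers to control of blood pressure generally. The avelumab cell has no such backstop.
- *Frequency is unknown.* Section 1.2.3 gives drug-related hypertension in 48% of regorafenib patients, which might suggest that the disputed cells will be used often. The figure is not split by grade, and Grades 1 and 2 require no avelumab change.

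**Conclusion.** The inconsistency in the avelumab column is real as written and nothing else in the protocol resolves it. It applies to Grade 4 hypertension occurring after the first avelumab dose. Investigator discretion reduces the practical risk but leaves the contradictory instruction in place.

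The overlap between the Grade 3 trigger and the restart condition is a weaker, secondary point. It affects asymptomatic patients graded on systolic pressure or treatment need whose diastolic pressure is already at or below 90 mmHg. It may follow from a deliberate diastolic target, but the hold is then empty for these patients and the text does not acknowledge it.

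Neither point can be sized: the protocol gives no Grade 3 or 4 frequency for hypertension and no split by systolic or diastolic trigger. No endpoint definition, sample size or error rate changes. It should be corrected because the fix is specific and cheap and bears on patient safety.

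**What to change.** The sponsor's clinical team should reconcile three cells of the Appendix 8 hypertension table by amendment:

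- the Grade 3 and Grade 4 avelumab cells with each other, so that the instruction at each grade is intended and, if they are meant to differ in this direction, the reason is stated;
- the Grade 3 trigger with the restart condition, in both the regorafenib and the avelumab cell, so that it is clear what a hold means for a patient graded on systolic pressure or on treatment need.

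Which rule applies is for the clinical team; none is proposed here. The cost is a small table correction and notice to sites, with no extra visits or data.

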| 2. Laboratory tests*             | 
 
Hematology: neutrophils, lymphocytes, basophils, eosinophils, monocytes, haemoglobin, platelet count, red blood cell count, total white cell count.
 
                                                                                                   | Up to 24 hours before Day 1 of cycle 1
Repeat on Days 8, 15 and 22 of Cycles 1 and 2
Thereafter, repeat before each Avelumab injection (ie. Day 1 and Day 15).
At discontinuation visit                                                                                                                                                                                                                                             |
|                                         | 
 
Biochemistry: Serum electrolytes (Na+, K+, Cl, P and Ca++), liver function tests (AST, ALT, total bilirubin, GGT and AP), LDH, creatinine, glucose, total proteins, urea, albumin, CPK, lipase, amylase.
 
 | Up to 24 hours before Day 1 of cycle 1
Repeat on Day 15 of Cycle 1
Repeat before each Avelumab injection (ie. Day 1 and Day 15).
At discontinuation visit
Note that hepatic tests (AST, ALT, GGT and alkaline phosphatase) must be also performed at Days 8 and 22 of cycles 1 and 2                                                                                                                                      |
|                                         | 
 
Thyroid test: 
 
All cohorts : TSH,
 
For cohort F only : Thyroglobulin and Antithyroglobulin antibody
 
 
 
                                                                                         | Up to 24 hours before Day 1 of cycle 1 
 
All cohorts : TSH : Repeat on Day 15 of Cycle 1, repeat on Day 1 and Day 15 of cycle 2, then on Day 1 of each subsequent cycle, at discontinuation visit and safety follow-up visit
 
For cohort F only : Thyroglobulin and Antithyroglobulin antibody : repeat on Day 1 every 2 cycles, at discontinuation visit and safety follow-up visit
 
 |

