| < 3 times upper limit of normal (ULN) for ALT/AST and/or total bilirubin > ULN to 1.5 x ULN | Any occurrence
Continue Regorafenib treatment.
Monitor liver function weekly until transaminases return to <3 times ULN or baseline                                                                                                                                                                                                         | Continue Avelumab therapy.
Continue liver function monitoring
If worsens:
Treat as appropriated ALT/AST increased (see below)                                                                                                                                                                                                                                                                                                                                                          |
| AST or ALT > 3.0 to ≤ 5 x ULN
and/or total bilirubin > 1.5 to ≤ 3 x ULN                  |                                                                                                                                                                                                                                                                                                                                                   | Withhold Avelumab therapy

Increase frequency of monitoring to every 3 days
If returns to <3 times ULN or baseline: resume routine monitoring, resume Avelumab therapy
If elevation persists > 5-7 days or worsens : treat as appropriated ALT/AST increased (see below)                                                                                                                                                                                                            |

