| AST or ALT > 5 x ULN to ≤20 x ULN and/or total bilirubin > 3 x ULN to ≤ 10 x ULN            | 1st occurrence :
Interrupt Regorafenib treatment.
Monitor transaminases weekly until return to <3 times ULN or baseline.
Restart: If the potential benefit outweighs the risk of hepatotoxicity, decrease dose by one dose level, and monitor liver function weekly for at least 4 weeks.

Re-occurrence : Discontinue permanently | discontinue Avelumab therapy

Increase frequency of monitoring to every 1 to 2 days
1 to 2 mg/kg/day prednisolone or equivalent

Add prophylactic antibiotics for opportunistic infections
Consult gastroenterologist / hepatologist
Consider obtaining MRI/CT scan of liver and liver biopsy if clinically warranted

If returns to <3 times ULN or baseline:
Taper steroids over at least 1 month
If does not improve in > 3 to 5 days, worsens or rebounds: |
| >20 times ULN
or >3 times ULN with concurrent bilirubin > 2 times ULN                    | Any occurrence
Discontinue permanently
Monitor liver function weekly until resolution or return to baseline.                                                                                                                                                                                                                                | Add mycophenolate mofetil 1 gram (g) twice daily
If no response within an additional 3 to 5 days , consider other immunosuppressants per local guidelines
Re-occurrence : Discontinue permanently                                                                                                                                                                                                                                                                                         |

a For cohort [A], regorafenib should be interrupted and no dose reduction are allowed. Patients requiring a delay of > 4 weeks should permanently discontinue regorafenib

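### Appendix 8 liver table, second row: the avelumab restart limit of < 3 x ULN suits AST/ALT but not bilirubin, whose hold band below 3.0 x ULN already meets it

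*Protocol*

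**What the plan says.** All in the Appendix 8 table on ALT, AST and bilirubin increases:

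- **First row.** Avelumab continues. The bilirubin part of this band is "and/or total bilirubin > ULN to 1.5 x ULN".
- **Second row, trigger.** Avelumab is withheld for AST or ALT above 3 and up to 5 x ULN "and/or total bilirubin > 1.5 to ≤ 3 x ULN". Either analyte is enough.
- **Second row, release.** Checks move to every 3 days, and then: "If returns to <3 times ULN or baseline: resume routine monitoring, resume Avelumab therapy".
- **Second row, escalation.** "If elevation persists > 5-7 days or worsens : treat as appropriated ALT/AST increased (see below").
- **Third row, where escalation leads.** Avelumab is discontinued and the patient receives "1 to 2 mg/kg/day prednisolone or equivalent".
- **Regorafenib column.** The same number appears with its analyte named: "Monitor liver function weekly until transaminases return to <3 times ULN or baseline".

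Elsewhere, inclusion criterion 9c (Section 4.1) caps total bilirubin at 1.5 x ULN at entry. Section 7.6.1 lets avelumab restart after an immune-related event at Grade 1 or less, and refers to Appendix 8 for management.

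**The concern.** A restart limit should lie below the level that caused the hold; otherwise the hold has no recovery condition. In this row one number serves two analytes whose hold bands differ. It is right for transaminases. For bilirubin, the value that stops avelumab also permits it to resume.

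The row also gives two instructions for the same patient. A bilirubin steady at about 2 x ULN meets the release limit at the first 3-day check. If it stays there beyond 5-7 days, it also fits the escalation line, which leads to discontinuation and steroids. Two sites could read the row differently. What is at stake is consistent handling of a hepatic safety rule, in a trial whose cohort D enrols biliary tract and hepatocellular cancers.

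**Working it through.** No sample size or error rate is involved. The check compares each hold band with the release limit.

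**Inputs** (Appendix 8 liver table, in multiples of ULN)

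| Analyte | Hold band, second row | Release limit as written | Overlap |
|---|---|---|---|
| AST/ALT | (3.0, 5.0] | [0, 3.0) | none |
| Total bilirubin | (1.5, 3.0] | [0, 3.0) | (1.5, 3.0) |

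**Grid check in steps of 0.01 x ULN**

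- Bilirubin, 1.51 to 3.00: 149 of 150 values are already < 3. The only exception is 3.00 itself.
- AST/ALT, 3.01 to 5.00: 0 of 200 values are < 3.

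**Example, bilirubin steady at 2.0 x ULN**

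- Hold: 1.5 < 2.0 ≤ 3.0, so avelumab is withheld.
- Release: 2.0 < 3.0, so the limit is met at the first 3-day check. That falls before the 5-7 day line can apply, since 3 < 5.
- Escalation: the same value, unchanged after 5-7 days, is a persisting elevation.

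**Does the baseline alternative tighten the limit?** No. It is joined by 'or', so < 3 x ULN alone is sufficient.

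**Does reading the limit as transaminases only repair the row?** Not fully. The regorafenib cells support that reading. But an isolated bilirubin rise would then have no numeric restart limit apart from return to baseline, and the cell does not say that this is meant.

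**Scope.** The fourth row takes over when transaminases exceed 3 x ULN together with bilirubin above 2 x ULN. The gap therefore concerns bilirubin rises without that combination.

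**Check of the remedy.** With a bilirubin limit of ≤ 1.5 x ULN, [0, 1.5] and (1.5, 3.0] do not overlap: 0 of 150 grid values qualify, so a real fall is needed. The value 1.5 is the top of the first-row band and the entry cap. It also follows the pattern of Appendix 8, where avelumab held for grade 2 diarrhoea, grade 2 pneumonitis or grade 2-3 creatinine rises resumes only at grade 1 or below.

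**The case against.** The strongest reply is that a sensible investigator would not restart. The cell speaks of a value that returns to the limit, and a steady 2 x ULN has not returned to anything. Read with the regorafenib column, transaminases go back below 3 x ULN and bilirubin goes back to baseline, which entry caps at 1.5 x ULN. That is plausible and close to the proposed fix, but the reader has to supply it. Section 7.6.1 points the same way with its Grade 1 limit, yet it covers immune-related events and refers back to Appendix 8.

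The controls outside the row carry more weight. Section 5.5 requires biochemistry, including total bilirubin, before each avelumab injection, so a bilirubin still in the band triggers the hold again. Section 7.6.1 also ends avelumab after two or more consecutive cancelled injections. If two successive holds count as cancellations, the site that chose to resume also reaches discontinuation. These points stand and limit the practical effect.

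A reader might infer a monitoring gap of a definite length, because release returns the patient to routine monitoring and the extra tests, "hepatic tests (AST, ALT, GGT and alkaline phosphatase) must be also performed at Days 8 and 22 of cycles 1 and 2", do not list bilirubin. The documents do not support a figure. Any such count assumes that the trigger was a scheduled Day 1 or Day 15 sample. It also sets aside the weekly liver-function monitoring in the regorafenib column. That cell stands in the first row, where transaminases are already below 3 x ULN, so it probably spans the first two rows, and Section 5.5 counts total bilirubin among the liver function tests. Its stopping point is tied to transaminases, so it is not a complete safeguard for an isolated bilirubin rise, but it cannot be ignored.

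**Conclusion.** The row is wrong as written. Its release limit fits AST/ALT and is empty for bilirubin over the whole hold band except the single value 3.0 x ULN, and the escalation line can apply to the same stable value. This rests only on the printed thresholds and on the row naming no analyte.

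Severity is minor. It would go too far to conclude that patients would repeatedly be infused at a bilirubin that requires a hold: the pre-infusion sample and the rule on cancelled injections stand in the way. What remains is a possible difference between sites in when monitoring is relaxed and whether steroids start. The protocol gives no frequency for isolated bilirubin rises, so none is assumed. No efficacy endpoint, decision rule or error rate is affected.

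**What to change.** In the second row, avelumab cell, replace the release condition with one that names both analytes: resume avelumab and routine monitoring only when AST and ALT are < 3 x ULN or baseline **and** total bilirubin is ≤ 1.5 x ULN or baseline. The sponsor should confirm the bilirubin value.

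The sponsor should also state whether the 5-7 day escalation applies to an isolated bilirubin elevation. The line now mentions only ALT/AST. Applying it to bilirubin would mean discontinuation and steroids for a persistent isolated rise, which is a clinical decision for the sponsor.

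Optionally, add a bilirubin recovery limit to the third-row regorafenib cell, which bilirubin alone can trigger but which follows only transaminases.

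The cost is wording in one table cell, plus the optional alignment. No visit or test is added.
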